## 14.3 Collection/follow-up of AE/ SAEs

### 14.3.1 Collection of AE/SAE

The collection of AE/SAE information shall begin from the signing of the ICF and continue until the end of the safety follow-up period (defined as 30 days after the last administration of the investigational product) or Screening failure, whichever occurs first.

If a study participant initiates new anti-tumor therapy prior to the completion of the safety follow-up period, only AE/SAEs suspected to be related to the investigational product shall be collected from the start of the new anti-tumor therapy until the end of the safety follow-up period.

Any death occurring during the safety follow-up period must be reported as an SAE, irrespective of whether the participant received other treatments.

For all AEs occurring in study participants, investigators must maintain detailed documentation including: AE name, Start and end dates, Severity grade, Relationship to the investigational product, Duration, Actions taken regarding the investigational product, Outcome and Whether the event meets SAE criteria.

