| Endpoints | 1. Primary Endpoints:  Incidence and frequency of Dose-Limiting Toxicity (DLT)  2. Secondary Endpoints:  (1) Adverse drug reactions;  (2) Recurrence-Free Survival (RFS);  (3) Disease Control Rate (DCR);  3. Tumor Response Evaluation (per RECIST 1.1 criteria):   - Complete Response (CR): Disappearance of all target lesions; no new lesions. - Partial Response (PR): ≥30% decrease in the sum of diameters of target lesions. - Stable Disease (SD): Neither sufficient shrinkage to qualify for PR nor sufficient increase to qualify for PD. - Progressive Disease (PD): ≥20% increase in the sum of diameters of target lesions or appearance of new lesions. |
| Study Procedures | 1. Arm A: TURBT unresectable  If the recurrent tumor can't be excised by TURBT, participants will be assigned to this arm. Participants in this arm will complete the neoadjuvant therapy with Irinotecan liposome (intravenous injection, once every two weeks for 1 month, dose increasing regimen: 37.6 mg/m^2^ and 56.5mg/m^2^) and Epirubicin (intravesical instillation, once a week for 1 month, 50 mg), and the therapeutic effect was evaluated by pelvic enhanced MRI and cystoscopy. Judged by two senior urologists, patients with complete response and partial response were treated with TURBT and intravesical therapy. Patients with stable disease or progressive disease received subsequent therapy at the investigator's discretion. Participants will visit the clinic once every 2 weeks for checkups and tests.  2. Arm B: TURBT resectable  If the recurrent tumor can be excised by TURBT, participants will be assigned to this arm (Arm B). Participants in this arm will complete TURBT with immediate intravesical instillation of Epirubicin (50 mg) within 24 hours after surgery. During the induction phase (the first 1 month after surgery), participants will receive the combined therapy with irinotecan liposome (intravenous injection, once every two weeks for 1 month, dose increasing regimen: 37.6 mg/m^2^ and 56.5mg/m^2^) and Epirubicin (intravesical instillation, once a week for 1 month, 50 mg). In the next 6 months, participants will continue the intravesical instillation treatment with Epirubicin (once a month, 50 mg). Participants will visit the clinic once every 2 weeks for checkups and tests in the first month, and once every 3 months after the first month. |

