## 4.1 Overall design

Enrolled patients with anthracycline-resistant recurrent NMIBC will first undergo enhanced pelvic-abdominal MRI and cystoscopy to collect imaging and pathological data. Two senior urologists will determine whether the tumor is resectable via TURBT. If unresectable (Arm A), patients will receive neoadjuvant irinotecan liposome combined with Epirubicin per the dose-escalation protocol. Post-treatment efficacy will be assessed by contrast-enhanced pelvic-abdominal MRI. For patients with CR and PR, TURBT with intravesical therapy was performed following confirmation by two independent senior urologists. For patients with SD or PD, subsequent therapies were determined by the investigator’s discretion. If resectable (Arm B), TURBT will be performed followed by immediate intravesical Epirubicin (50 mg) instillation within 24 hours postoperatively. During the induction phase (weeks 1-4 post-TURBT), the treatment with irinotecan liposome combined with Epirubicin will be completed according to the dose - escalation regimen. During the maintenance phase (months 1-6 post-TURBT), intravesical maintenance instillation of Epirubicin will be conducted once a month for a total of 6 cycles. The safety and adverse reactions will be followed up from the induction phase, and the tumor recurrence will be assessed by pelvic and abdominal enhanced MRI and cystoscopy after combination treatment.

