## 4.4 Treatment Period Follow-up

Arm A: routine blood test, liver and kidney function, coagulation function and adverse reactions were followed up every cycle after the first cycle of Irinotecan liposomal treatment. Pelvic and abdominal enhanced MRI and cystoscopy were performed after the second cycle of irinotecan liposomal treatment. The patients who achieved CR and PR were treated with TURBT combined with intravesical therapy after judged by two senior urologists. Patients with SD or PD received subsequent therapy at the investigator's discretion.

Arm B: Routine blood test, liver and kidney function, coagulation function and adverse reactions were followed up every cycle after the first cycle of Irinotecan liposomal treatment. Pelvic and abdominal enhanced MRI and cystoscopy were performed after combination treatment.

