## 4.5 Safety Evaluation

The safety analysis will summarize drug exposure (including duration and dose) and adverse events (AEs) based on the safety analysis set population. The investigator is responsible for monitoring the safety of all subjects enrolled in this study, documenting any AEs, including: Serious adverse events (SAEs), Treatment-emergent adverse events (TEAEs) of Grade ≥3, TEAEs leading to treatment discontinuation or dose interruption/reduction/delay.

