## 12.4 Safety Follow-up

The follow-up shall be conducted at 7 days (±2 days) after the last dose of study medication and includes the following:

- Adverse event assessment;
- Documentation of concomitant medications and concomitant therapies;
- Recording of subsequent anti-tumor therapies.

Collection of adverse events begins from the signing of the ICF and continues until the end of the safety follow-up period (i.e., 7 days after the last administration of the study drug or upon screening failure).If a study participant initiates new anti-tumor therapy before the end of the safety follow-up period, only AEs/SAEs suspected to be related to the study drug will be collected from the start of the new anti-tumor therapy until the end of the safety follow-up period. Any death occurring during the safety follow-up period must be reported as an SAE, regardless of whether the participant received other treatments.

After the safety follow-up period, only SAEs considered to be related to the investigational drug will be collected. For participants following the last dose of Irinotecan liposome, clinical follow-up or telephone visits will be conducted to collect information on survival status, AEs, concomitant medications, and concomitant therapies. Investigators may schedule additional visits as needed to follow up on the resolution of AEs.

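### AE collection is tied to the last dose and narrows at an undefined trigger, so all-cause capture of harms after the planned TURBT in Arm A, the only neoadjuvant arm, is at best partial

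*Protocol*

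**What the plan says.** **Close of collection.** AE collection starts when the consent form is signed. Section 12.4 says it "continues until the end of the safety follow-up period (i.e., 7 days after the last administration of the study drug". Section 14.3.1 runs it to "the end of the safety follow-up period (defined as 30 days after the last administration of the investigational product". The two figures conflict.

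**Narrowing.** Both sections restrict collection if another anti-tumour treatment starts before the close. Section 14.3.1 puts it this way: "only AE/SAEs suspected to be related to the investigational product shall be collected from the start of the new anti-tumor therapy". What counts as new is not defined.

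**After the close.** Section 12.4 keeps only SAEs judged related to the drug. It also mentions clinic or telephone contacts that gather AEs, with no schedule or end date.

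**Arm A.** Pelvic and abdominal MRI and cystoscopy follow the second irinotecan liposome cycle. Section 4.4 continues: "The patients who achieved CR and PR were treated with TURBT combined with intravesical therapy after judged by two senior urologists". There is no date for this TURBT, no maximum interval, no safety visit after it, and no name for the intravesical agent.

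**Arm B.** TURBT comes first. Section 4.1 states: "If resectable (Arm B), TURBT will be performed followed by immediate intravesical Epirubicin (50 mg) instillation within 24 hours postoperatively". Four weeks of induction and six monthly instillations follow. The same section says that safety follow-up begins with the induction phase, which in Arm B is after TURBT.

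**Objective.** Section 2.1 puts the safety and tolerability of the neoadjuvant combination first.

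**The concern.** A window anchored to the last dose suits a regimen that ends with dosing. In Arm A the sequence ends with an operation. Bleeding, infection or slow recovery after TURBT, possibly made worse by recent cytopenia, is a main safety question for any neoadjuvant treatment, and only Arm A can answer it here. If the window closes before or shortly after surgery, or narrows on the day of surgery, such events are recorded only when an investigator in an open-label study suspects the drug.

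This is a matter of data collection. Events that were not recorded cannot be recovered in the analysis, so a later statistical analysis plan cannot repair it. The arm is also small. Section 5 plans 6 to 9 participants, so one participant with a missed complication is between 1/9 = 11% and 1/6 = 17% of Arm A.

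**Working it through.** The protocol states no coverage figure to reproduce. The check is calendar arithmetic.

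**Inputs**
- Day 1 is the first irinotecan liposome infusion. Dosing every two weeks for one month (section 4.2) gives days 1 and 15.
- Weekly epirubicin for one month gives days 1, 8, 15 and 22. The last is 1 + 3 × 7 = 22.
- With two-week cycles, cycle 2 ends on day 28, so the assessment falls on day 29 at the earliest.
- TURBT follows the assessment. Since no date is given, I take days 29, 36, 43, 50 and 57 as a range.
- The close is 7 days (section 12.4; its visit tolerance is ±2 days) or 30 days (section 14.3.1) after the last dose.
- Section 3.2 treats both drugs as investigational, while the synopsis lists only irinotecan liposome as study drug. Both anchors are therefore shown.

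**Formulas.** Close = last dose day + window length. Days of cover after TURBT = max(0, close − TURBT day).

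**Close in Arm A**
- Epirubicin anchor: 22 + 7 = day 29 (27 to 31 with the tolerance); 22 + 30 = day 52.
- Irinotecan anchor: 15 + 7 = day 22 (20 to 24); 15 + 30 = day 45.

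**Days of all-cause cover after TURBT in Arm A, if TURBT does not trigger the narrowing**

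| TURBT on day | 7-day text, epirubicin | 7-day text, irinotecan | 30-day text, epirubicin | 30-day text, irinotecan |
| --- | --- | --- | --- | --- |
| 29 | 0 (2 with tolerance) | 0 | 23 | 16 |
| 36 | 0 | 0 | 16 | 9 |
| 43 | 0 | 0 | 9 | 2 |
| 50 | 0 | 0 | 2 | 0 |
| 57 | 0 | 0 | 0 | 0 |

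If TURBT does count as new anti-tumour therapy, every cell becomes 0 for all-cause events, and only suspected-related events are kept from the day of surgery.

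**Arm B.** TURBT follows consent and precedes the study dosing. With the last maintenance instillation about 6 to 7 months later (30-day months, so day 180 to 210 after TURBT), the close lies between 180 + 7 = day 187 and 210 + 30 = day 240. Under sections 12.4 and 14.3.1 the 30 days after TURBT lie wholly inside the window. Under section 4.1, read literally, follow-up starts only after that TURBT.

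**The case against.** The strongest reply has four parts.

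1. The 30-day text gives up to 23 days of cover when TURBT is prompt. TURBT with intravesical therapy for responders is written into the protocol, so it is not naturally new therapy. This stands. A reader might infer that perioperative harms are largely missed in Arm A, or that every Arm A participant meets the narrowing trigger. The first needs the 7-day text, a late operation, or a strained reading of the trigger. The second merges two groups: participants with SD or PD may start other therapy, but no TURBT is planned for them.

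2. The Arm B side of the contrast is not secure. Section 4.1 starts safety follow-up at induction, and section 14.1.1 links AEs in time to use of the product. A reader might infer that all TURBT events in Arm B are kept. Sections 12.4 and 14.3.1 support that; section 4.1 contradicts it.

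3. If the intravesical agent after TURBT in Arm A is epirubicin given as study drug, the last dose moves and the window extends past surgery. This is possible, but the agent is not named.

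4. Some events are still caught: suspected-related AEs after narrowing, all deaths within the window, related SAEs afterwards, and whatever the unscheduled contacts bring in. Section 14.3.2 also has investigators ask about all AEs at each scheduled visit. These soften the gap. They do not close it, because no visit is scheduled after Arm A's TURBT for AEs, and the two-monthly contacts in section 12.5 collect recurrence and treatment information.

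**Conclusion.** The point holds as a gap in ascertainment. Counted from the neoadjuvant doses, no reading of the text gives Arm A a full 30 days of all-cause AE cover after its planned TURBT. Cover is about 0 to 2 days under section 12.4 and at most about 23 days under section 14.3.1, falling to 0 once TURBT is on day 52 or later (day 45 if the last irinotecan infusion is the anchor). These figures rest on the assumed dosing days and on TURBT no earlier than day 29. The 30-day yardstick borrows the length of the section 14.3.1 window. The gap concerns only participants with CR or PR among the 6 to 9 in Arm A.

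A reader might go further and infer that the safety summary will make Arm A look safer, since section 4.5 says "The safety analysis will summarize drug exposure (including duration and dose) and adverse events (AEs) based on the safety analysis set population" and Arm B is observed for longer. The documents do not support that. Section 4.5 names a population and does not say that the arms will only be pooled, no test of AEs between arms is planned, and by-arm or by-period tables are commonly left to a statistical analysis plan.

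The change is worth making before enrolment goes further: the first objective depends on these data and the remedy is cheap.

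**What to change.** 1. Reconcile sections 4.1, 12.4 and 14.3.1 so that AE collection has one start and one end. This settles both the 7-day versus 30-day conflict and the conflict between consent and induction as the starting point.
2. In sections 12.4 and 14.3.1, state that protocol TURBT with intravesical therapy in Arm A is not new anti-tumour therapy for the purpose of the narrowing rule.
3. For Arm A participants who go to TURBT, continue all-cause AE and SAE collection until 30 days after it.

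The cost is a short amendment to the AE paragraphs and the one sentence in section 4.1, plus AE recording for about 30 days after an operation the protocol already plans. The clinic or telephone contacts that section 12.4 already foresees can carry it. No extra participants, procedures or treatment changes are needed. The downside is a few more AE entries and a somewhat higher reported AE rate in Arm A.

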### 14.3.2 Follow-up of AE/SAE

Investigators shall inquire about all AE/SAEs occurring since the previous visit during each scheduled study visit and promptly provide follow-up information as required by any data queries received.

All AE/ SAEs should be followed until symptoms resolve, or clinically relevant changes in laboratory values return to baseline and/or ≤ grade 1, or have a reasonable explanation (e.g., loss to follow-up, death), or until the event is conclusively confirmed to be unrelated to the study drug or study procedure at the end of the safety follow-up period.

## 14.4 Abnormal liver function

If AST and/or ALT levels are abnormal and the TBIL level is abnormally increased, and the following conditions are met and there are no other reasons for the abnormality, the SAE reporting procedure should be followed.

| conditions | criteria |
| --- | --- |
| (1) Abnormal ALT or AST | Normal baseline: ALT or AST > 3× upper limit of normal (ULN) during treatment;  Abnormal baseline: ALT or AST > 2× baseline level and value > 3× ULN during treatment; Or > 8× ULN; |
| (2) Abnormal TBIL | Normal baseline: TBIL > 2×ULN during treatment;  Abnormal baseline: TBIL increased > 1×ULN or its value > 3×ULN during treatment; |
| (3) No hemolysis and alkaline phosphatase < 2×ULN (or information not available) | |

Participants who had an abnormal AST and/or ALT level combined with an abnormally elevated total bilirubin level during the safety follow-up period were advised to return to the study center for evaluation and confirmation as soon as the abnormal result was known, preferably within 48 hours.

## 14.5 SAE Reporting Procedure

Upon occurrence of an SAE, whether for initial reporting or follow-up reporting, the investigator must immediately complete, sign, and date a Serious Adverse Event/Adverse Event Report Form of special Interest and report it to the appropriate authorities

All SAEs should be recorded in detail, including symptoms, severity (according to CTCAE 5.0), correlation with each study drug, occurrence time, treatment time, measures taken for each study drug due to SAEs, follow-up time and methods, and outcome. If an SAE is considered by the investigator to be unrelated to the study drug but potentially related to study conditions (e.g., discontinuation of the original treatment, or coexisting conditions during the course of the trial), this relationship should be detailed in the narrative section of the SAE report form. If the intensity of an ongoing SAE or its relationship to the study drug changes, a follow-up report should be submitted immediately. If investigators believed that the previously reported SAEs were misreported, they could provide corrections, retractions, or de-escalation instructions in the follow-up report and report them according to SAE reporting procedures.

## 14.6 Disease Progression and Death

Disease progression is defined as the worsening of a participant's condition due to the studied indication, including radiological progression as well as progression of clinical symptoms and signs. The appearance of new metastatic lesions from the primary tumor or progression of existing metastases is considered disease progression.

In the study population of this trial, "disease progression" is an expected outcome and should not be reported as an AE term. When disease progression occurs, the events used to confirm progression should be reported as AEs. For example, if a participant experiences seizures determined to be related to brain metastases, the AE term should be recorded as "seizures" rather than "disease progression" or "brain metastases."

Similarly, events leading to the diagnosis of disease progression—even if they meet criteria such as being life-threatening, requiring hospitalization or prolonging hospitalization, or causing permanent or severe disability/functional impairment (significant limitation in the ability to perform normal life functions)—should not be reported as SAEs. However, if it is uncertain whether the AE is due to disease progression, it should be reported as an SAE.

During the safety follow-up period, deaths assessed by the investigator as potentially caused by symptoms or signs of disease progression must be reported as SAEs.

The term "death" should not be used as an SAE term but rather as an outcome. The adverse event that caused or led to death should be recorded as the SAE term. If the cause of death cannot be determined at the time of reporting, the SAE term should be recorded as "death of unknown cause."

## 14.7 Pregnancy

If the pregnancy is an ectopic pregnancy, spontaneous abortion, intrauterine fetal death, neonatal death, or congenital abnormality, it is considered to be an SAE and needs to be reported according to the reporting procedures of the SAE.

# 15. Data Management and Statistical Analysis

15. 1 Documentation of Source Record**s**

As the original documentation for clinical trials, source medical records and data files shall be completely preserved. The investigator is responsible for completing and maintaining these records. Prior to each entry, the participant information on the medical record cover must be verified. All entries shall be written legibly in clear and readable handwriting.

## 15. 2 CRF Design and Completion

The CRF is designed based on the clinical trial protocol and undergoes joint review by data managers, statisticians, investigators, and medical personnel. The final version of the CRF must be approved by the investigator prior to use. The CRF design must comply with the protocol and adhere to relevant laws and regulations to ensure the collection of all clinical data required by the trial protocol.

The CRF is to be completed by the investigator, and a CRF must be fully filled out for each enrolled participant.

## 15. 3 Monitoring and Auditing of Data

Monitoring Content:

- Compliance with the trial protocol;
- Identification and correction of any data errors or omissions;
- Verification of data authenticity and completeness, a process also referred to as Source Data Verification (SDV).

## 15.4 Recording and Retention of Research Data

To facilitate subsequent evaluation and oversight by relevant authorities, investigators shall retain all study documentation, including verification records for all study participants (enabling effective cross-checking of all records, such as original hospital documentation). The retention period shall be 5 years after study completion or until the investigator determines the materials may be destroyed, whichever occurs later.

## 15.5 Statistical Analysis

### 15.5.1 Analysis datasets

(1) Full Analysis Set (FAS):

The Full Analysis Set (FAS) consists of all study participants who signed the ICF, were enrolled in the study, and received at least one dose of the investigational drug. The FAS serves as the primary analysis set for efficacy endpoints in this study. For cases where the full treatment course was not observed, the last observation carried forward (LOCF) method will be applied to impute missing data for the final analysis.

(2) Per-protocol set (PPS):

PPS will be defined as all subjects who met the trial protocol, did not take prohibited drugs, with favorable compliance, and completed CRF. No imputation of missing data. Efficacy analysis was conducted based on PPS populations.

(3) Safety analysis set (SS):

The SS population will serve as the population for the safety analysis. All randomized subjects have received at least one dose of the research drug and have a post-administration safety record.

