## 3.2 Secondary Endpoints

(1) Adverse drug reactions: Any noxious, unintended response to the investigational drug(s) (Irinotecan liposome + Epirubicin) at any dose, causally related to treatment (per WHO-UMC causality assessment criteria).

(2) Recurrence-Free Survival (RFS): Time from treatment initiation to histologically confirmed tumor recurrence, radiologic progression or death from any cause.

(3) Disease Control Rate (DCR): Proportion of patients achieving complete response (CR), partial response (PR) and stable disease (SD).

Note: Tumor Response Evaluation (per RECIST 1.1 criteria):

- CR: Disappearance of all target lesions; no new lesions.
- PR: ≥30% decrease in the sum of diameters of target lesions.
- SD: Neither sufficient shrinkage to qualify for PR nor sufficient increase to qualify for progressive disease (PD).
- PD: ≥20% increase in the sum of diameters of target lesions or appearance of new lesions.

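### LOCF in the full analysis set is not limited to post-baseline values, so an Arm A participant with no post-treatment tumour assessment can count as stable disease and raise the disease control rate

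*Protocol*

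**What the plan says.** Protocol section 15.5.1 admits to the FAS every enrolled participant who "received at least one dose of the investigational drug"; no post-baseline tumour assessment is required. It then says: "The FAS serves as the primary analysis set for efficacy endpoints in this study". The missing-data rule follows directly and is aimed at participants whose course of treatment is incompletely observed; for them, "the last observation carried forward (LOCF) method will be applied to impute missing data for the final analysis". The same section describes a per-protocol set (PPS) without imputation and adds: "Efficacy analysis was conducted based on PPS populations".

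Section 3.2 defines the DCR as the share of participants with CR, PR or SD. SD is a residual class, with no minimum duration: "Neither sufficient shrinkage to qualify for PR nor sufficient increase to qualify for progressive disease (PD"). PR needs a decrease of at least 30% in the sum of diameters. PD needs an increase of at least 20% or a new lesion. There is no not-evaluable category.

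Section 6.1 requires measurable disease at entry, and section 12.1 lists a screening pelvic MRI. For Arm A, section 4.4 names one response time point: "Pelvic and abdominal enhanced MRI and cystoscopy were performed after the second cycle of irinotecan liposomal treatment". Section 12.3 lists tumour imaging within 3 days of confirmed treatment discontinuation, and section 6.3 asks participants who stop treatment to complete their remaining visits.

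**The concern.** LOCF needs an earlier observation to carry. With one named response time point, an Arm A participant who misses it and has no discontinuation scan has only the screening measurement. Carrying that forward asserts that the tumour did not change, and the residual definition of SD turns the assertion into disease control.

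The error runs one way: a carried-forward baseline can never be PD. It also falls on people who may well have done badly, such as those who died, were lost, refused imaging, or stopped for clinical deterioration without a scan. A participant who dies unscanned would be an event for recurrence-free survival (RFS), because section 3.2 includes death from any cause, yet could count as controlled in the DCR. In an arm of 6 to 9, one or two such participants visibly change the reported rate.

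**Working it through.** **Inputs.** Arm size n = 6 to 9 (section 5). Response limits: decrease of at least 30% for PR, increase of at least 20% or a new lesion for PD (section 3.2). The protocol gives no expected DCR and no dropout rate, so the counts m and p below are assumptions.

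**The plan's own figure.** 2 × 6 = 12 and 2 × 9 = 18, which agrees with the stated total of 12 to 18.

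**Step 1: class of a carried-forward baseline.** Change = (baseline − baseline) / baseline = 0%. This reaches neither the −30% nor the +20% limit, so the class is SD whatever the baseline size. The result was the same for sums of 10, 15, 30 and 60 mm.

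**Step 2: three ways of computing DCR.** Let m be the number with no post-baseline assessment and p the number scanned with PD. All other scanned participants are controlled: c = n − m − p.

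- LOCF: (c + m) / n
- Missing counted as not controlled: c / n
- Assessed only: c / (n − m)

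LOCF minus not-controlled is m / n. For one participant that is 1/9 = 11.1 points to 1/6 = 16.7 points.

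LOCF minus assessed-only is p/(n − m) − p/n = pm / [n(n − m)]. This is smaller than m / n whenever any scanned participant is controlled, and is zero when p = 0.

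**Step 3: hypothetical cases, with Clopper-Pearson 95% intervals.** The protocol names that method for the DLT rate only; using it for DCR is an assumption.

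| n | m | p | LOCF | Not controlled | Assessed only |
|---|---|---|---|---|---|
| 6 | 1 | 1 | 5/6 = 83.3% (35.9–99.6) | 4/6 = 66.7% (22.3–95.7) | 4/5 = 80.0% (28.4–99.5) |
| 6 | 2 | 2 | 4/6 = 66.7% (22.3–95.7) | 2/6 = 33.3% (4.3–77.7) | 2/4 = 50.0% (6.8–93.2) |
| 6 | 2 | 0 | 6/6 = 100% (54.1–100) | 4/6 = 66.7% (22.3–95.7) | 4/4 = 100% (39.8–100) |
| 9 | 1 | 1 | 8/9 = 88.9% (51.8–99.7) | 7/9 = 77.8% (40.0–97.2) | 7/8 = 87.5% (47.3–99.7) |
| 9 | 2 | 2 | 7/9 = 77.8% (40.0–97.2) | 5/9 = 55.6% (21.2–86.3) | 5/7 = 71.4% (29.0–96.3) |

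In the second row the formula gives 2 × 2 / (6 × 4) = 16.7 points between LOCF and assessed-only, which matches 66.7% − 50.0%. In the third row the point estimate equals the assessed-only one, but LOCF still narrows the interval by treating unobserved participants as observed.

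**The case against.** The strongest reply is that the protocol never says an unscanned participant is SD. If LOCF acts on response categories, such a participant has no earlier category to carry and stays missing. That is a fair reading and the text does not exclude it. It does not rescue the rule, because nothing limits LOCF to post-baseline values, and under this reading the FAS has no stated handling for that participant.

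Second, few participants may be affected. Combination treatment lasts about one month, sections 6.3 and 12.3 call for continued visits and a discontinuation scan, section 12.2 lists tumour imaging during treatment, and section 12.6 allows unscheduled imaging. This stands as a limit on size. It does not cover death, loss to follow-up or refusal, and section 12 describes all examinations as recommended and open to modification.

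A reader might infer more than the documents support:

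- That every early stop becomes a success. It does not. Progression that ends treatment under section 6.3 is RECIST-confirmed, so the value carried forward is PD.
- That RFS is imputed as free of recurrence. Section 15.5.3 specifies Kaplan-Meier for RFS, and nothing says that a recurrence-free status is carried forward.
- That the PPS sentence displaces the FAS. Section 15.5.1 already names the FAS as primary for efficacy; what is missing is a label for the role of the PPS.
- That Arm B is affected in the same way. There TURBT removes the lesions, so a carried-forward pre-operative measurement would have little meaning as a response.

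**Conclusion.** The point holds for Arm A DCR, and only for FAS participants with no post-baseline tumour assessment. For them, unrestricted LOCF combined with the section 3.2 definitions yields disease control without evidence. The shift per participant follows from the planned arm sizes and does not depend on a dropout rate; how many participants are affected is unknown. The two-unscanned cases are illustrations, not forecasts, and at these arm sizes the intervals overlap heavily under every rule.

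Severity is moderate. DCR is a secondary endpoint. The primary DLT analysis uses its own analysis set, and neither it nor the escalation decisions depend on this rule. The point still merits correction before the efficacy data are analysed, because the bias cannot run against the regimen and section 15.5.3 plans to report DCR with a confidence interval and a between-group test.

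**What to change.** In section 15.5.1:

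1. Delete LOCF for tumour response.
2. State that FAS participants with no evaluable post-baseline tumour assessment stay in the DCR denominator as not controlled, and report how many there are and why.
3. Report the assessed-only DCR as a sensitivity analysis. Counting missing as not controlled is deliberately conservative, and the two figures together show how much the result depends on it.
4. Label the PPS efficacy analysis as supportive to the FAS.
5. State that LOCF does not apply to the Kaplan-Meier analysis of RFS.

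The cost is a few sentences, with no new data and no change to treatment or visits. The downside is that the reported DCR may be lower: by m/n compared with LOCF on the baseline value, and not at all if every Arm A participant is scanned.
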